#### Technical aspects of the mHealth platform

Melon Health’s platform is built to maximise patient confidentiality and general security of the application at all levels. The system exceeds New Zealand privacy requirements and meets US HIPAA (Health Insurance Portability and Accountability Act) security rules for health data, with regular auditing by external security specialists.

The platform currently integrates with over 350 wearables and biometric sensors through its open API (application programming interface), and platform is accessible through a web-based application or Android/iOS applications.

### Control arm

Participants in the control arm will receive usual care. Although this may vary somewhat between practices and GPs, the key interest is the extent to which the BetaMe programme may improve outcomes beyond that expected in the context of usual care. For people with T2DM, this would typically involve an annual diabetes review to monitor glycaemic control and assess the patient for the presence of any diabetes complications and a review of treatment. In addition, it could include education and advice on lifestyle factors, such as diet and exercise, provided by a trained practice nurse or diabetes specialist nurse. For people with pre-diabetes, usual care would typically include lifestyle advice and education about diet and exercise, and an annual HbA1c.

The study team will also provide participants in the control arm with standard information about pre-diabetes and T2DM and its management, from resources produced and provided by Diabetes NZ (Pamphlets entitled ‘Pre-diabetes’, ‘Diabetes and Healthy Food Choices’, and ‘Live Well with Diabetes’, available at https://www.diabetes.org.nz/pamphlet-ordering/). This is to increase retention of control arm participants in the study, and to ensure that all patients have basic information on T2DM and pre-diabetes.

### Randomisation and blinding

Based upon their baseline HbA1c test results (pre-diabetes or diabetes range), participants will be randomised into the intervention or control arm (1:1 allocation) using a computer-generated randomisation schedule stratified by participating practice and ethnicity (and separate for the two HbA1c-level groups). Randomisation will be completed within two working days of the completed baseline assessment. To ensure allocation concealment, randomisation will be centrally determined from within the REDCap electronic data capture platform *after* the patient is enrolled in the study (following the first assessment with the research nurse and when full eligibility based on current HbA1c level has been determined). To ensure balance in numbers allocated to each study arm, randomisation lists will be blocked.

The randomisation allocation list will not be visible to the team member(s) requesting the allocation, and this team member(s) will only have details on the patient ID, practice, and ethnicity when requesting allocation for any patient. The exact length of each randomisation block will be kept in a separate document held by the principal investigator (PI), project manager and project statistician, and thus will not be available to the team member(s) responsible for determining allocation.

Given the nature of the intervention, it is not possible to keep participants blind to their intervention status. Research nurses taking objective measurements will be kept blind to the intervention status of participants to the extent possible. However, when the nurse meets with the participant at the 4- and 12-month follow-up visits, it is not possible to guarantee that the nurses remain blind to the intervention allocation of the participant. The results dataset will be stored with the study arm identity blinded by code. The key to this code will be held independent of the analysis dataset by the PI, a second member of the research team (MM), and an independent member of the internal Data Monitoring Group. Data cleaning and analysis will be conducted by a statistician who is blind to group allocation. Once analysis is complete, the results will be unblinded.

### Outcome measures

The co-primary outcomes are changes in HbA1c and weight at 12 months. HbA1c provides the most sensitive measure of glycaemic control among those with T2DM. High levels are predictive of higher levels of complications and mortality. Weight (and waist circumference) are associated with T2DM, cardiovascular disease, several cancers and overall mortality [28–30]. We will focus on weight in kilograms as this is the most common outcome in systematic [31, 32] and Cochrane reviews, [33, 34] but for completeness we will also report differences in units of Body Mass Index (BMI).

Secondary outcomes are:Change in waist circumference at 12 monthsChange in blood pressure at 12 months. High blood pressure (common amongst people with diabetes) is associated with a higher risk of cardiovascular disease and mortality, and is amenable to lifestyle interventions [35, 36]

Additional self-reported outcomes include:Medications (regular prescription medications), and changes to medications and dosesChanges in self-management of chronic conditions using the Partners in Health Scale. This is a validated tool for self-reported self-management of chronic conditions [37]Diabetes-specific behaviours and outcomes will be measured using two validated instruments: the Summary of Diabetes Self-Care Activities tool, which assesses participants’ self-care activities [38]; and the Diabetes Distress Scale which differentiates those with high and low levels of distress [39]Health-related quality of life measured using the five-level EuroQol five dimensions questionnaire (EQ-5D-5 L) [40]. Short-term outcomes: we will assess primary and secondary outcomes at 4 months. This will give an indication of the effect of the ‘active’ part of the intervention. Research has shown that even short-term decreases in HbA1c can have a long-term effect on health outcomes, with effects tending to attenuate over time [12, 13, 41]

Outcomes will be assessed for all participants (regardless of whether they complete the intervention) by trained nurses at baseline, 4 months and 12 months (Tables 2 and 3).

### Sample size and analysis

All primary analyses will be based on intention-to-treat principles (with individuals analysed in the group to which they were randomised). Demographic and baseline characteristics will be summarised using descriptive statistics. Both HbA1c and weight will be analysed as continuous variables. For the HbA1c primary outcome, analysis will be conducted both combined and separately for pre-diabetes and T2DM. For weight, the primary analysis will combine participants with pre-diabetes and T2DM. Analysis will use linear mixed models, comparing mean outcome levels between intervention and control arms at the 12-month endpoint, adjusted for initial HbA1c level (accounting for baseline differences in outcome) and for other important baseline covariates (age, gender, ethnicity, weight). This analysis will include the 4-month measurements, providing some information for those individuals subsequently lost to follow-up and hence missing final outcome data (mixed models analysis treats these final data as missing at random conditional on baseline and intermediate covariates, i.e. these individuals are expected on average to have final outcomes similar to other people with the same baseline covariates and HbA1c trajectories). As the study involves repeated measures data, these models will include random effects for individuals to account for correlation between measurements from the same person at different follow-up times.

The study is powered in the pre-diabetes group to detect a difference of 2.5 mmol/mol between study arms (80% power, alpha = 0.05, presuming SD = 5.5 mmol/mol [42]). This requires a sample size of 76 per study arm (152 total). In the pilot study, the mean reduction in HbA1c was 2.6 mmol/mol. The sample size for the T2DM group is powered to detect a minimal clinically important difference [43, 44] of 5.5 mmol/mol between study arms (80% power, alpha for comparison = 0.05, presuming a standard deviation of 15 mmol/mol in this group [16]). This requires a sample size of 117 per study arm (234 total). This gives a combined sample size of 386 people with pre-diabetes and people with T2DM. To account for loss of precision due to patients lost to follow-up (projected at 10% [45, 46]), we will recruit 430 patients at baseline (note that all participants will be included in linear mixed models analysis, even if missing final endpoint data, which reduces bias in estimating effect size, but there is still loss in statistical power compared to having complete follow-up data).

Analysis of weight differences between study arms will use the same analytical methods as for the HbA1c outcome. For these weight analyses, those with pre-diabetes and T2DM will be pooled prior to analysis as the relevant intervention target weight loss is the same for these two groups. Analysis will be stratified on patient group to account for the pooled approach, and we will also report weight differences by study arm within each patient group. The comparison of weight loss in the combined patient group is powered to detect a difference between study arms of 5 kg (80% power, alpha = 0.05, SD = 15 kg in this group [47]). This requires a sample size of 142 per study arm (284 total), which is within the combined sample size calculated for the HbA1c outcome.

We will also estimate differences in HbA1c and weight endpoints by study arm for each of the stratified randomisation ethnic groups (Māori, Pacific, other ethnicities), and will report the mean intervention effect and 95% confidence interval for each group. Proportions of patients meeting HbA1c and weight-loss targets will also be analysed by ethnic group with logistic regression (adjusted for baseline covariates), and adjusted absolute risk differences in treatment outcomes will be computed to quantify treatment effectiveness [48]. Assuming that 20% of the sample will be Māori (*n* = 234 × 0.2 = 46 Māori participants) gives an anticipated margin of error on the intervention effect of ± 4.5 mmol/mol for HbA1c in the diabetic group.

Analysis of self-reported outcomes will be conducted in a similar way.

Results will be actively disseminated (see Additional file 3).

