The BetaMe intervention consists of four separate components; health coaches, provision of evidence-based educational resources, goal tracking and peer support:Health coaching. The health coaches are all either qualified personal trainers or registered nurses trained in motivational interviewing, cognitive behavioural therapy, and nutrition, and have completed the Heart Foundation Pacific Heartbeat Community Nutrition course. Health coaches arrange an initial one-on-one session with participants. The purpose of this first 1 h session is for health coaches to work with participants to develop goals tailored to their needs and values. The session follows a set format. Māori and Pacific coaches are available. Once these goals have been set and agreed on, participants’ goals are entered into their profile on the BetaMe system. Coaches will continue to work with participants, and will message participants weekly to check on their progress, reinforce information from the modules and arrange further meetings at frequencies that suit the participant (these can be weekly, fortnightly or less frequently if preferred). These subsequent meetings are generally around 15–20 min in length. All meetings with the coaches will be by audio or video, as per the participant’s preference. Support and clinical governance of the health coaches is provided by a clinical psychologist, general practitioner and an experienced health coach. Coaches also regularly interact with one another via an online forum (separate from patient forums) to share any problems they are having and solutionsHealth literacy component. There are eight key education modules introduced to participants via the web and mobile platform with attached resources (videos, infographics, articles, tips, tools, meal ideas and mini-quiz). The key messages in the modules are reinforced in corresponding email newsletters, discussions on the newsfeed initiated by the community manager and by the participant’s coach. Every 2 weeks, a new module is released that presents participants with a range of topics that offer key messages to help them to learn about and manage their own health. The modules cover risk factors for T2DM and pre-diabetes, healthy eating and physical activity, identifying triggers for less healthy decisions and establishing healthy habits, sleep and shift work, meal planning, problem solving, healthy coping and mindfulness (see Additional file 2 for more information)Goal tracking. Participants are encouraged to track their progress towards their goals (including healthy eating, physical activity, weight, happiness and sleep). They will be provided with a set of digital scales and a tape measure so they can take their own measurements and track their progress. They will be able to share these data with their health coach at any time, or with their physician by email or at their next appointmentPeer support. The programme also includes peer support with real-time chat within a private and secure online social network monitored by a community manager who is a registered nurse trained in nutrition. This person monitors the community to ensure nothing unsafe (like personal details, or negative health messages) is shared, and that people are supported and supportive. They will also reinforce key messages, highlight local events in the area, start conversations and welcome new people to the community. The community manager also provides a point of contact for both technical support, and for support more generally, particularly after the first 16 weeks of the programme when the health coaching module is completed.

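### Practice is a stratification factor but is missing from the stated primary models, and the combined HbA1c model has no HbA1c-level-group term; the effect is small and conservative, and possible coach clustering merits a sensitivity analysis

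*Protocol article*

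**What the plan says.** **Design.** Under Randomisation and blinding, participants are individually allocated 1:1 in blocks, using a "randomisation schedule stratified by participating practice and ethnicity (and separate for the two HbA1c-level groups"). There are thus three factors: practice, ethnicity and HbA1c-level group.

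**Model.** Under Sample size and analysis, the 12-month comparison comes from linear mixed models "adjusted for initial HbA1c level (accounting for baseline differences in outcome) and for other important baseline covariates (age, gender, ethnicity, weight"). On random effects, the text says that "these models will include random effects for individuals to account for correlation between measurements from the same person at different follow-up times". Practice and coach are not mentioned anywhere in that section.

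**HbA1c-level group.** For HbA1c, "analysis will be conducted both combined and separately for pre-diabetes and T2DM". The weight analysis pools the two patient groups, uses the same methods as HbA1c, and is stratified on patient group.

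**Coaching.** The Intervention arm section describes one-on-one coaching in that arm only: "Coaches will continue to work with participants, and will message participants weekly". The number of coaches and their caseloads are not stated.

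**The concern.** When allocation is balanced within a factor that predicts outcome, the analysis should carry that factor. Otherwise its variance stays in the error term and the standard error of the arm difference is overstated. The stated model keeps ethnicity and drops practice, although the Control arm section accepts that usual care differs between practices. The HbA1c comparisons are sized for only 80% power, so precision already earned by the design should not be given away.

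A second question concerns dependence in one arm only. Participants who share a coach may have correlated outcomes, and the control arm has no counterpart. A random effect for the individual describes repeated measurements on one person and cannot absorb this. If such correlation exists at 12 months, the modelled standard error is too small.

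**Working it through.** **1. The plan's own sample sizes.** With n per arm = 2(1.960 + 0.842)² SD²/δ², where (1.960 + 0.842)² ≈ 7.849:
- Pre-diabetes HbA1c: 2 × 7.849 × 5.5²/2.5² = 76.0, stated 76.
- T2DM HbA1c: 2 × 7.849 × 15²/5.5² = 116.8, stated 117.
- Weight: 2 × 7.849 × 15²/5² = 141.3, stated 142.
- Total: 152 + 234 = 386, and 386/0.9 = 429 against 430 stated.

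All reproduce. All treat participants as independent, with no term for practice or coach.

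**2. Which factors reach which model**

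| Randomisation factor | HbA1c, separate by group | HbA1c, combined | Weight, pooled |
|---|---|---|---|
| Ethnicity | covariate | covariate | covariate |
| HbA1c-level group | constant within each analysis | no explicit term; continuous initial HbA1c only | stratified on patient group |
| Practice | absent | absent | absent |

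**3. Leaving practice out.** The protocol gives no practice ICC, so 0.01 to 0.10 is assumed. With arms balanced within practice, between-practice variance cancels from the arm difference but stays in the modelled error. So modelled SE / true SE = 1/√(1 − ICC), and actual alpha = 2[1 − Φ(1.96 × ratio)].

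| Practice ICC | SE ratio | Actual alpha |
|---|---|---|
| 0.01 | 1.005 | 0.049 |
| 0.02 | 1.010 | 0.048 |
| 0.05 | 1.026 | 0.044 |
| 0.10 | 1.054 | 0.039 |

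Expressed in participants, the same reported precision could be had from 386 × (1 − ICC) people with practice modelled: 382 at ICC 0.01 and 347 at ICC 0.10.

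**4. Leaving coach out.** Caseload m and coach ICC are also assumptions. With clustering in one arm, DE = 1 + (m − 1) × ICC, true SE / modelled SE = √((1 + DE)/2), and actual alpha = 2[1 − Φ(1.96/ratio)].

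| m | Coach ICC | DE | SE ratio | Actual alpha |
|---|---|---|---|---|
| 15 | 0.01 | 1.14 | 1.034 | 0.058 |
| 20 | 0.02 | 1.38 | 1.091 | 0.072 |
| 20 | 0.05 | 1.95 | 1.214 | 0.107 |

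The answer depends heavily on the unknown number of coaches. Over 5 to 20 coaches and ICC 0.01 to 0.05, alpha runs from 0.052 (pre-diabetes, 76 per arm, 20 coaches, ICC 0.01) to 0.159 (pooled weight, 193 per arm, 5 coaches, ICC 0.05).

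**5. Simulation under no average effect.** This used 400 participants, 20 practices, 10 coaches, 4,000 runs and a comparison ignoring both levels. Monte Carlo error is about √(0.05 × 0.95/4000) = 0.003.

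| Practice ICC | Coach ICC | Rejection rate |
|---|---|---|
| 0 | 0 | 0.052 |
| 0.05 | 0 | 0.043 |
| 0.10 | 0 | 0.043 |
| 0 | 0.02 | 0.065 |
| 0 | 0.05 | 0.108 |
| 0.05 | 0.05 | 0.103 |

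The directions agree with the formulas: the practice omission is conservative and the coach omission is anti-conservative.

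**The case against.** **The text is a condensed article.** It says individual random effects will be included, not that no others will be, and it refers to a fuller protocol held at the registry. This stands as a caution. But the article does list its covariates, and that list includes one stratification factor and omits another, so the model as published does not match the design.

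**HbA1c-level group is not ignored.** A reader might infer that the primary models omit it altogether. The text does not support that. The HbA1c sample sizes rest on the separate group analyses, where group is constant; weight is stratified on patient group; and continuous initial HbA1c takes up much of the factor in the combined HbA1c model. Only the explicit term in that one model is lacking.

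**The practice effect is small and safe.** This is correct. The relevant ICC is also what remains after covariate adjustment, so the upper end may be generous. Many small blocked strata may also leave balance within practice only approximate, which would shrink the overstatement further.

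**The coach effect is conjectural.** This is largely accepted. Coaching ends at week 16 and the endpoint is at 12 months; the first session has a fixed structure; coaches share governance; modules and forum are common to all. If the programme helped nobody, coaches could not differ in effect, so the inflation concerns an average effect of zero with real differences between coaches. A reader might infer that type I error is known to be about 11%; nothing in the protocol establishes that.

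**The two errors may cancel.** They can: 1.034/1.026 = 1.008 at practice ICC 0.05 and coach m = 15, ICC 0.01. They need not: with both ICCs at 0.05, the simulated error was 0.103.

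**Conclusion.** The point holds in limited form. Practice is a randomisation factor and is absent from every stated primary model; HbA1c-level group lacks an explicit term only in the combined HbA1c model. For practice the consequence is a standard error about 0.5% to 5% too large and an actual alpha of about 0.049 to 0.039. This assumes a practice ICC of 0.01 to 0.10 and balance within practice. It costs precision and does not create false positives, so it is no threat to validity, but it is worth correcting because the correction is nearly free.

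Coach clustering is a separate possibility working in the other direction. Its size cannot be determined from the protocol; the 6% to 11% range is illustrative and rests wholly on the assumed caseloads and ICCs. It justifies a sensitivity analysis, not a change to the primary model.

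**What to change.** 1. Add a random intercept for practice to all primary HbA1c and weight models, alongside the random effect for the individual.
2. In the combined HbA1c model, add HbA1c-level group as a fixed effect, using the group applied at randomisation. This needs stating because the Participants section classifies patients partly by recorded diagnosis, whereas randomisation goes by baseline HbA1c range, so the two may differ for some people.
3. Pre-specify a sensitivity analysis with a coach-level random effect for intervention participants only (partially nested, with small-sample degrees of freedom), and report the number of coaches and their caseloads.

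The first two are changes of wording: practice and HbA1c are held in REDCap and re-checked before randomisation. The third needs coach assignments, which the programme provider should be able to supply since coaches log their contacts. It may widen the interval. It also has a cost for blinding: a coach identifier exists only in the intervention arm and so reveals allocation, while the protocol keeps the analysing statistician blind. It should therefore be linked and run only after the blinded primary analysis is complete.

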Change in blood pressure	At 4 and 12 months	Measured using a calibrated syphgmomanometer using a standard approach (blood pressure taken when participant has been sitting quietly for 5 min, without eating, drinking or smoking. They will be asked to have feet flat on the floor, with their back up against the back of the chair, and their left arm straight on the table). Three measures will be taken with the lowest of the last two measures recorded
Change in self-management	At 4 and 12 months	Measured using the Partners in Health Scale [37]
Change of score in diabetic-specific behaviours and outcomes	At 4 and 12 months	Measured using the Summary of Diabetes Self-Care Activities tool, which assess participants’ self-care activities [38]
Health-related quality of life	At 4 and 12 months	Measured using the five-level EuroQol five dimensions questionnaire (EQ-5D-5 L)
Change in score of diabetes-specific outcomes	At 4 and 12 months	Measured using the Diabetes Distress Scale [39]
Change in dose of insulin	At 4 months relative to baseline, and 12 months relative to 4 months	Categorised as (1) starting insulin in current time period; (2) increasing dose of insulin in current period; (3) reducing dose of insulin in current period or (4) stopping insulin in current period. Data will be collected from patients, verified where possible from clinic records
Change in dose of metformin	At 4 months relative to baseline, and 12 months relative to 4 months	Categorised as (1) starting metformin in current time period; (2) increasing dose of metformin in current period; (3) reducing dose of metformin in current period or (4) stopping metformin in current period. Data will be collected from patients, verified where possible from clinic records
Change in dose of other oral hypoglycaemic agents (not metformin)	At 4 months relative to baseline, and 12 months relative to 4 months	Categorised as (1) starting oral hypoglycaemic agents in current time period; (2) increasing dose of oral hypoglycaemic agents in current period; (3) reducing dose of oral hypoglycaemic agents in current period or (4) stopping oral hypoglycaemic agents in current period. Data will be collected from patients, verified where possible from clinic records

*EDTA* ethylenediaminetetracetic acid, *HbA1c* glycosylated haemoglobin, *HPLC* high-performance liquid chromatography

^a^All time periods are time after recruitment, and compared with baseline with exception of changes in medication dose specified above

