**Table 3 Tab3:** Summary of variables measured in the patient questionnaire

Measure	Details	Source
Baseline patient demographic questions	Name, address, date of birth, ethnicity	All questions are based upon Statistics New Zealand census questions: available from: http://archive.stats.govt.nz/methods/classifications-and-standards/classification-related-stats-standards/gender-identity.aspx?_ga=2.83660500.398110315.1519357080-701333020.1444617687
Smoking question	To ascertain current, never and ex-smokers	Parts of the New Zealand Health Survey smoking panel Ministry of Health. 2015. Adult Questionnaire (Year 5) 1 July 2015 to 30 June 2016: New Zealand Health Survey. Wellington: Ministry of Health. Available from: http://www.health.govt.nz/publication/questionnaires-and-content-guide-2014-15-new-zealand-health-survey
Healthcare utilisation questions	Primary care, afterhours, Emergency Department ED and hospital admissions	Modified from the New Zealand Health Survey Ministry of Health. 2015. Adult Questionnaire (Year 5) 1 July 2015–30 June 2016: New Zealand Health Survey. Wellington: Ministry of Health. Available from: http://www.health.govt.nz/publication/questionnaires-and-content-guide-2014-15-new-zealand-health-survey
Comorbid conditions questions	List of conditions	List is a modified version of: Sanga O, Stucki G, Liang M, Fossel AH, Katz JN. The Self-Administered Comorbidity Questionnaire: a new method to assess comorbidity for clinical and health services research. *Arthritis Rheum* 2003; 49: 156–63. [62]
Medication questions	Name, dose and frequency	Questions developed by research team.
Health-related quality of life (EQ-5D-5 L)	Health profile and Visual Analogue Scale rating	Permission granted to use the paper and REDCap versions of the EQ-5D-5 L. Available from: https://euroqol.org/eq-5d-instruments/eq-5d-5l-about/

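### The HbA1c model leaves recorded baseline glucose-lowering treatment out of its covariates, which costs some precision but causes no bias

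*Protocol article*

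**What the plan says.** All places are in the Protocol article.

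- **Sample size and analysis, HbA1c model.** A linear mixed model compares the arms at 12 months. It adjusts for initial HbA1c and "for other important baseline covariates (age, gender, ethnicity, weight". The list is written out, and glucose-lowering treatment is not in it.
- **Sample size and analysis, principle.** "All primary analyses will be based on intention-to-treat principles (with individuals analysed in the group to which they were randomised".
- **Sample size and analysis, targets.** "Proportions of patients meeting HbA1c and weight-loss targets will also be analysed by ethnic group with logistic regression (adjusted for baseline covariates". The HbA1c target is not defined and these covariates are not named.
- **Randomisation and blinding.** Strata are practice and ethnicity, with separate lists for the two HbA1c ranges. Drug treatment is not a stratum. Participants are not blinded.
- **Participants.** Current insulin treatment bars entry; no oral agent does.
- **Table 3.** The medication questions record "Name, dose and frequency".
- **Table 2.** Changes in insulin, metformin and other oral agents are secondary outcomes. The metformin row reads "Categorised as (1) starting metformin in current time period; (2) increasing dose of metformin in current period", and goes on to reductions and stops. The first change is measured from baseline to 4 months, so a baseline drug record must exist.

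**The concern.** Two participants with T2DM and the same initial HbA1c may differ in expected 12-month HbA1c if one is on no drug and the other is on two oral agents. Neither initial HbA1c nor the HbA1c-range strata show whether a value was reached on or off treatment. Baseline treatment is therefore a plausible prognostic factor. It is fixed before randomisation and already collected, yet it is absent from a covariate list that the article itself spells out.

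Precision is what is at stake. The T2DM comparison is planned at exactly 80% power with a large assumed SD (15 mmol/mol), so a cheap reduction in residual variance is worth having. Treatment is likely to vary most in this group. The combined HbA1c analysis contains the same participants.

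**Working it through.** **Inputs from Sample size and analysis:** T2DM difference 5.5 mmol/mol, SD 15 mmol/mol, alpha 0.05, power 80%, 117 per arm. Allocation is 1:1 (Randomisation and blinding). A two-sided test and the normal approximation are assumed.

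**Step 1. Reproduce the plan's figure.**
n per arm = 2 × (1.960 + 0.842)² × SD² / difference² = 2 × 7.85 × 225 / 30.25 = 116.8, so 117. This agrees with the article. The pre-diabetes figure (2.5 mmol/mol, SD 5.5) also reproduces at 76 per arm. The total is (76 + 117) × 2 = 386, and 386 / 0.9 = 429 against 430 stated. The sample size is not in question.

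**Step 2. Add a prognostic baseline covariate.**
Let R² be the share of the remaining HbA1c variance that baseline treatment explains. The residual SD becomes 15 × √(1 − R²), and power is Φ(5.5 / [SD × √(2/117)] − 1.96). The article gives no value of R², so a range of 0.02 to 0.10 is assumed.

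| Assumed R² | Residual SD | Power at 117 per arm | n per arm for 80% |
|---|---|---|---|
| 0 | 15.00 | 80% | 117 |
| 0.02 | 14.85 | 80.9% | 115 |
| 0.05 | 14.62 | 82.1% | 111 |
| 0.10 | 14.23 | 84.0% | 106 |

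The planning SD of 15 is used as the residual SD before treatment is added. If the covariates already listed reduce it, power starts above 80% and the gain in percentage points is smaller.

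**Step 3. Cost if treatment explains nothing.**
A three-level factor uses two parameters among 234 participants with T2DM. 2 / 234 is under 1%, so little is lost.

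**Step 4. Bias.**
Baseline treatment precedes randomisation, so any imbalance between arms is due to chance. Leaving it out of a linear model leaves the arm difference unbiased and affects only its variance.

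**The case against.** The strongest reply is that this is a preference, not an error. Any prognostic variable left out of a model gives up precision, the model already adjusts for initial HbA1c, and the R² range has no support in the article. This stands in part. The gain is small and its size is assumed. The point is kept because the list is fixed in the article, the variable is already collected, and the change costs almost nothing.

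A reader might infer more, and the article does not support it:

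- **That a participant who reaches the HbA1c target after a drug start or increase counts as a success.** This is a natural reading under intention-to-treat, but it rests on silence. The target, its covariates and any drug rule may be set in the full protocol or the analysis plan, which are not shown.
- **That unequal drug changes distort the HbA1c contrast.** If escalation differed by 10 percentage points and each escalation lowered HbA1c by 5 to 10 mmol/mol, the T2DM mean difference would move by 0.10 × 5 = 0.5 to 0.10 × 10 = 1.0 mmol/mol. That is 9% to 18% of 5.5, in either direction. The article gives neither input. The trial also asks what the programme adds to usual care, and Control arm says usual care in T2DM typically includes "a review of treatment". Later prescribing is part of that comparison. Sharing tracked data with a physician belongs to the intervention (Intervention arm, goal tracking).
- **That drugs are disregarded.** Insulin users are excluded at entry, and changes in three drug classes are secondary outcomes.

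**Conclusion.** The point holds as a modest matter of efficiency. The HbA1c covariate list omits baseline glucose-lowering treatment, which is recorded, unstratified and free to vary among participants with T2DM who are not on insulin. Including it would raise T2DM power at 117 per arm from 80% to about 81% to 84%, equivalent to needing 115 down to 106 per arm. This rests on an assumed partial R² of 0.02 to 0.10 and the planning SD of 15 mmol/mol.

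The randomised comparison is not biased by the omission. The intention-to-treat mean difference, regardless of later drug changes, is a valid answer to the question the trial poses. Nothing here calls for adjusting it for drug changes after randomisation, which allocation may itself affect.

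**What to change.** 1. In Sample size and analysis, add baseline glucose-lowering treatment (none; metformin only; any other oral agent) to the HbA1c model covariates for the T2DM and combined analyses, and settle this before unblinding. The cost is two parameters, one line of text and some coding of the medication data.
2. Keep the intention-to-treat mean difference as primary, and state that HbA1c is analysed regardless of later drug changes.
3. Optionally, as a supplementary result only, report by arm the proportion meeting the HbA1c target with no start or dose increase of a glucose-lowering drug since baseline. Place it next to the plain target analysis and the drug-change outcomes already planned. Its limits should be stated: it depends on prescribing after randomisation, which allocation may influence, and on drug data that come from unblinded participants and are checked against clinic records only where possible. It would also score as a failure an intervention participant whose shared data prompted treatment.
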